### Screening for eligibility and recruitment {15}

A GCP trained research midwife will assess the eligibility of patients to participate in the study according to inclusion/exclusion criteria using screening form.

### Ineligible and non-recruited participants

Certain ineligible are stated in the exclusion criteria. Research midwives/clinician will review and reassess each potential participant and confirm eligibility of patients to participate in the study at the day of CS.

### Patient consent {26a}

A suitably qualified research midwife or doctor who is also part of the clinical care team will introduce the study to the woman at their pre-operative assessment. A participant information sheet (PIS) will be provided to facilitate this process. Investigators will ensure that they adequately explain the aim, anticipated benefits and potential hazards of taking part in the trial to the woman. They will also stress that participation is voluntary and that the woman is free to refuse to take part and may withdraw from the trial at any time. The woman will be given adequate time to read the PIS and to discuss their potential participation and be given the opportunity to ask questions. If the woman expresses an interest in participating in the trial, they will be asked to sign and date the latest version of the informed consent form at least 24 h prior to CS. The woman will be asked for her consent to withdraw 3 blood samples (with a maximum volume of 10 mL blood per sample) and 2 fat tissues and for collection of outcome data from their medical records and a telephone interview at 30–40 days post-natal that will take approximately 5–15 min.

### Withdrawal of study participants

Each participant has the right to withdraw from the study at any time and this will not affect their clinical care. In addition, the investigator may discontinue a participant from the study at any time if the investigator considers it necessary for any reason including the following:
Ineligibility (either arising during the study or retrospectively having been overlooked at screening)Withdrawal of consent

Withdrawal from the study will result in the exclusion of the data for that participant from analysis; provided that the withdrawal occurs within 3 months of data collection.

### Study assessments {13}

The study assessment and paperwork associated are summarised in Table 3 (forms are in the online supplementary file).

**Table 3 Tab3:** Schedule of assessments and associated paperwork

Visit	Screening form	Consent form	Baseline form	Eligibility reassessment form	CS procedure form	Collection and labelling of samples	Discharge form	Follow-up interview form	Medical record check form
Eligibility check	×								
Consent at least 24 h pre-CS		×	×	×					
Day of CS until discharge					×	×	×		
Follow-up								×	×

### Data collection methods {18a}

Background information will be collected from each participant using the baseline form. This information is required for interpretation of the data and dissemination.

Following the collection of the data from all forms (screening, consent, baseline, eligibility reassessment, operation, discharge, follow-up interview, 6-week record check) will be filled, signed and shared via the secure system; this system can be accessed at the university and the hospital and ensures the security of data, any data, entered will be anonymised.

The study has two parts: part A, which is blood and adipose tissue sampling for cefuroxime concentrations; part B, is a follow-up of patients’ post-partum at between 30 and 40 days to record the incidence of post-surgical infection.

#### Part A: Sample collection at caesarean section

The clinical care team will record the time of cefuroxime administration, dose administered, type of anaesthesia used, blood loss and other relevant clinical information. Five samples will be collected: 1 blood sample at time of skin incision, 1 blood sample at time of skin closure, 1 blood sample at recovery room (< 3 h following CS), 1 adipose tissue sample (approximately 1 cm from the skin in the middle of the Pfannesnstiel or vertical midline incision) at skin incision and one adipose tissue sample (from a similar location to sample 1) just prior to skin closure.

### Blood sample and adipose tissue analysis

The concentration of cefuroxime in blood and adipose tissue will be quantified using standard laboratory methods [15].

#### Part B: Follow-up for post-surgical infection

At between 30 and 40 days post-CS, the study participants will be contacted by telephone by a research nurse/midwife from the research team and a review will be made to record any type of post-surgical infection. The follow-up interview form will be used to record the details of any infection reported. If the participant attended to the hospital for a post-natal appointment at 30–40 days, the interview can be conducted at that time to minimise the burden to the participant.

### Plans to promote participant retention and complete follow-up {18b}

Patient medical notes will be reviewed by a member of the clinical care team using the 30–40 days outcome form to identify whether there has been a reported post-surgical infection. Post-surgical infection is defined as per the definitions set out by the US Centre’s for Disease Control and Prevention [14].

### Data management {19} and confidentiality {27}

All participants will be given a study ID upon recruitment to the study. A spreadsheet that links study ID to patient ID will be held at Birmingham Women’s and Children’s Hospital NHS Foundation Trust under the control of the local PI. This information will be password protected and stored on an encrypted computer that conforms to the standard NHS security requirements.

The study ID will be used on all forms; this information provides anonymised data to the University of Birmingham that no longer has any personal identifiable data. Following collection the data from all forms will be entered on a secure system at the NHS site (undertaken by the research midwife); this system can be accessed at the university and ensures anonymity for the participants.

All processes will be carried out with respect to participant confidentiality. All participant data will be anonymised by being replaced with a study ID number prior to data sharing with the University of Birmingham. The anonymity code will only be known to the local site PI and associated research nurse/midwife team. The data will be controlled by usernames and encrypted passwords.

### Statistics {20a}, sample size {14} and study assessment

There is no predefined sample size yet sufficient numbers are required to provide an estimate of average values as well as the level of inter-patient variability. Previous work to measure the concentration of antibiotics in plasma and in tissue in obese and non-obese pregnant women following CS has used sample sizes of 14 in each arm to detect differences in adipose antibiotic concentration [16, 17]. Therefore, in this study, we plan to recruit 15 women in each arm (BMI < 30 kg/m^2^ and BMI ≥ 30 kg/m^2^). The BMI measurements will be taken from the women at their time of booking appointment which occurs between 10 and 14 weeks of pregnancy. The BMI of participants immediately prior to CS will be determined to review any major changes during their pregnancy which may affect the results, for example, a change from < 30 kg/m^2^ to an extremely obese participant at CS.

The differences in mean concentration values in plasma and adipose tissue between the obese and non-obese populations will be compared using ANOVA analysis to determine whether there are significant differences. SPSS software will be used for all statistical analysis. The rate and type of infection will be analysed. The rate of infections will be analysed in correlation with (1) dose administered, (2) BMI and (3) cefuroxime concentrations at both sites at the time of skin incision and skin closure.

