**Methods:**

This study plans to compare maternal cefuroxime concentrations (plasma and adipose tissue), at the time of skin incision and time of skin closure during a caesarean section from non-obese (body mass index BMI < 30 kg/m^2^) and obese (BMI ≥ 30 kg/m^2^) pregnant women. The incidence of post-surgical site infection will also be measured. At least 15 participants are required for each arm (non-obese vs obese) with a total of 30 participants. The study participants will be followed up between 30 and 40 days post-caesarean section to record details of any post-caesarean surgical infection to explore correlations between BMI, measured cefuroxime concentrations and post-caesarean infection rates.

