**Discussion:**

This pilot study will allow the development of a model testing the inter-patient variability in plasma and adipose tissue concentrations of cefuroxime. The results will facilitate the development of a larger study to determine whether differences in cefuroxime plasma and tissue concentration in obese and non-obese women can support the development of a physiologically based pharmacokinetic model. This model can then be used to propose dosing adjustments that can be used in a further trial to optimise cefuroxime dosing for women undergoing caesarean section.

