### Participant selection and enrolment

Any patient (18–50 years) who requires a CS as part of their clinical care will be screened for inclusion. The potential participants will be identified using hospital clinical lists, where lists relate to a pre-booked CS a Good Clinical Practice (GCP) trained research midwife who is a member of the clinical care team will assess the eligibility of patients to participate in the study according to inclusion/exclusion criteria using screening form. The woman will then be provided with the participant information sheet at this meeting by the research midwife. In addition, if a pregnant woman is booked for CS at a meeting they may be informed about the study by a research midwife or their clinical care team and provided with a participant information sheet. The participants will receive information about the study well in advance (at prior clinic appointments) and at least 24 hours prior to CS so that all participants have sufficient time to consider taking part.

This study plans to compare data from obese (BMI ≥ 30 kg/m^2^) and non-obese women (BMI < 30 kg/m^2^) at the time of booking (10–14 weeks of pregnancy). At least 15 participants are required for each arm with a total of 30 participants. The study sequence is summarised in Table 2.

**Table 2 Tab2:** Summary of the C-LACE study sequence and methodology

Timing	Activity
Caesarean section booking clinic	Clinic list will be reviewed for eligible participants using the screening form
On the day of caesarean section	A Venflon cannula will be inserted into the woman as part of the research process to enable withdrawal of the required blood samples without the need for additional needles. This second access point will ensure that the blood sampling is minimally disruptive to the CS procedure.
At 30–40 days post-caesarean section	Participant’s medical file and notes will be reviewed by the research midwife to identify any post-surgical site infection which will be recorded on the 6-week outcome form. Research midwife will attempt to contact the participant 3 times between 30 and 40 days post-CS to complete the follow-up interview form.
Samples analysis	Blood and adipose tissue will be analysed by LC-MS/MS [15]

*GCP* Good Clinical Practice, *CS* Caesarean section, *LC-MS/MS* liquid Chromatography with tandem mass spectrometry

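### The ANOVA named for cefuroxime concentrations gives no sampling point and no woman effect, although each woman supplies up to three plasma and two adipose samples; a mixed model per matrix would be the better choice

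*Protocol article*

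**What the plan says.** Under Part A: Sample collection at caesarean section, the protocol article says "Five samples will be collected: 1 blood sample at time of skin incision, 1 blood sample at time of skin closure, 1 blood sample at" the recovery room, within 3 hours of surgery. Adipose tissue is taken "at skin incision and one adipose tissue sample (from a similar location to sample 1) just prior to skin closure". The consent section gives the same count: "withdraw 3 blood samples (with a maximum volume of 10 mL blood per sample) and 2 fat tissues".

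The sample size is counted in women: "we plan to recruit 15 women in each arm", 30 in total.

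For the concentrations, the section Statistics {20a}, sample size {14} and study assessment names one method: "The differences in mean concentration values in plasma and adipose tissue between the obese and non-obese populations will be compared using ANOVA analysis", run in SPSS. The factor named is BMI group. The type of ANOVA, the sampling points that enter it and the handling of several samples from one woman are not given. The abstract frames the comparison as "at the time of skin incision and time of skin closure during a caesarean section", and the aims use the same two times. The abstract also says the pilot will allow "development of a model testing the inter-patient variability in plasma and adipose tissue concentrations of cefuroxime".

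**The concern.** The woman is the unit that is grouped, and the sample is the unit that is measured. Samples from one woman are likely to be correlated. A comparison of group means that takes every sample as a separate observation would have 45 against 45 plasma values, or 30 against 30 adipose values, from only 15 against 15 women. Its standard error would then be wrong.

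Obese versus non-obese is a stated objective, and the ANOVA is meant to decide whether the differences are significant. The study also wants inter-patient variability for planning a larger study. A pooled ANOVA would mix variation between women with variation within a woman.

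**Working it through.** **Inputs from the documents.** 15 women per arm (2 × 15 = 30, as stated). Samples per woman, m: 2 adipose, 3 plasma. The article gives no significance level, SD or within-woman correlation. The size rests on precedent (14 per arm), so no stated power figure can be reproduced.

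**Assumptions.** Two-sided 5%; log concentrations normal with total SD 1; the same correlation ρ between any two samples of one woman in one matrix, with ρ from 0.3 to 0.7.

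**Reading 1: all samples pooled as independent, no change over time.** The variance of a group mean is understated by the design effect DE = 1 + (m − 1)ρ, so type I error ≈ 2 × [1 − Φ(1.96/√DE)]. The last column is a simulation of 20,000 null trials.

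| Matrix | ρ | DE | Formula | Simulated |
|---|---|---|---|---|
| Adipose (m = 2) | 0.3 | 1.3 | 8.6% | 8.8% |
| | 0.5 | 1.5 | 11.0% | 11.3% |
| | 0.7 | 1.7 | 13.3% | 13.6% |
| Plasma (m = 3) | 0.3 | 1.6 | 12.1% | 12.3% |
| | 0.5 | 2.0 | 16.6% | 17.0% |
| | 0.7 | 2.4 | 20.6% | 20.9% |

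If only incision and closure enter, as the abstract suggests, plasma also has m = 2 and the adipose rows apply to it.

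**Reading 1 with a decline that is not modelled.** If levels fall by s SD per sampling point, the fall enters the error term and adds V = s²(m² − 1)/12. Type I error ≈ 2 × [1 − Φ(1.96 × √((1 + V)/DE))]. At ρ = 0.5:

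- s = 1, adipose: V = 0.25, and 1.96 × √(1.25/1.5) = 1.789, giving 7.4% (simulated 7.2%).
- s = 1, plasma: V = 0.667, and 1.96 × √(1.667/2) = 1.789, giving 7.4% (simulated 7.5%).
- s = 3, adipose: V = 2.25, and 1.96 × √(3.25/1.5) = 2.885, giving 0.4% (simulated 0.3%).
- s = 3, plasma: V = 6, giving 0.02% (simulated 0.01%).

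Over ρ = 0.3–0.7 the simulated range is 4.7–10.2% for s = 1 and 0.0–0.6% for s = 3. The error can go either way.

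**Reading 2: a separate ANOVA at each sampling point.** There is one value per woman, and simulated type I error is about 5% for each test. If all sampling points are tested at ρ = 0.5, at least one false difference arises in about 12.5% of trials for plasma and 9% for adipose.

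Power for an assumed difference of 1 SD, the same at every sampling point, at ρ = 0.5: the variance of a woman's mean is [1 + (m − 1)ρ]/m, which is 1 for one sample, 0.75 for two and 0.667 for three. The standardised differences are 1.00, 1.15 and 1.22. With 28 degrees of freedom, the noncentral t distribution gives 75%, 86% and 90%.

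**Reading 3: classical repeated-measures ANOVA.** With complete data the group test is valid, because it equals a test on the women's means (simulated type I error about 5%). The usual form drops any woman without a full set. The success criteria accept full collection in 75% of each arm: 0.75 × 15 = 11.25, so 12 of 15 women would suffice and up to 3 per arm could be lost. The missing-data section says the main analysis uses the available data.

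**The case against.** A reader might infer that the plan states an ordinary ANOVA with samples treated as independent, and that false positives will be far above 5%. The document does not support this. It says ANOVA without a type, a term that also covers a repeated-measures ANOVA or one ANOVA per sampling point, and both are valid for the group comparison. It never says that samples are pooled. The abstract and the aims name incision and closure, and the infection analysis keeps those times apart, all of which fits separate valid tests. Even under pooling, the inflated rates need a weak or absent time trend. That is doubtful when the dose precedes incision and plasma sampling runs into recovery.

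A reader might also infer that inter-patient variability cannot be estimated on any reading. That goes too far: with one value per woman, the within-group SD describes the spread between women at that time. What it cannot do is separate stable differences between women from variation within a woman.

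The article condenses a fuller protocol that may specify the ANOVA, so the missing detail is not itself a fault. The main objective is feasibility, and the success criteria use no p-value.

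All of this stands, and it limits the severity. What remains is that the article does name a method, and on each reading of it a better one is available for the same data.

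**Conclusion.** The concern holds as a modest improvement to a loosely stated method. It is not a demonstrated error in a declared analysis. Pooling would put the type I error at about 9–14% (adipose) or 12–21% (plasma) for ρ of 0.3–0.7 with no time trend, and possibly below 5% with a steep decline. Separate tests are valid but have 75% power against 86–90% for an analysis that uses all of a woman's samples. Classical repeated-measures ANOVA conflicts with the available-data rule once samples are missing.

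The correlations, the time trends and the 1 SD difference are assumptions, since the article gives none. The power gain also needs a group effect that is constant over sampling points, and the 90% needs all three plasma samples in the comparison.

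**What to change.** In the statistics section, replace the ANOVA wording with: for each matrix (plasma, adipose), a linear mixed model on log concentration with BMI group, sampling point and their interaction as fixed effects and woman as a random effect. Report the group contrast as a geometric mean ratio with 95% CI at incision and at closure, the times named in the abstract, and also averaged over sampling points. Report the between-woman and within-woman variances from the same model.

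This uses samples the study will collect anyway, and SPSS, which the article names, fits it under MIXED. It keeps women with an incomplete set in the analysis. The cost is slightly more analysis work and, compared with a pooled ANOVA, possibly fewer nominally significant results.

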### Trial design {8}

A single-centre experimental, prospective pilot study with non-probability sampling.

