## Methods/design

### Aims and methodologies

To measure cefuroxime concentration in plasma and adipose tissue (within the incision) at time of skin incision and skin closure in obese and non-obese pregnant patients requiring CS. Moreover, to explore the relationship between the dose of cefuroxime administered and concentration measured in both blood and adipose tissue with respect to BMI of the patient. To measure the incidence of post-CS infections in obese and non-obese pregnant women at 30–40 days post-CS; and to assess if the rate of infection is correlated with BMI, dose administered and cefuroxime blood or adipose tissue concentrations.

Cefuroxime is administrated to pregnant women undergoing CS as per Birmingham Women’s Hospital protocol; i.e. IV infusion 30–60 min before skin incision.

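### The ANOVA of mean cefuroxime concentrations has no term for time since dose, so it cannot separate an effect of obesity from a difference in sampling time

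*Protocol article*

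**What the plan says.** All references are to the protocol article.

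- **Analysis** (Statistics {20a}, sample size {14} and study assessment): "The differences in mean concentration values in plasma and adipose tissue between the obese and non-obese populations will be compared using ANOVA analysis". The purpose given is to find significant differences. No covariate or time term is named. Dose enters that section only in the planned correlation with infection.
- **Dosing** (Aims and methodologies): cefuroxime is given as "IV infusion 30–60 min before skin incision".
- **Sampling** (Part A: Sample collection at caesarean section): blood is taken as "1 blood sample at time of skin incision, 1 blood sample at time of skin closure, 1 blood sample at recovery room (< 3 h", the limit being counted after the section. Adipose tissue is taken at incision, followed by "one adipose tissue sample (from a similar location to sample 1) just prior to skin closure".
- **Recording** (same section): "The clinical care team will record the time of cefuroxime administration, dose administered" and other clinical details.
- **Design** (Trial design {8}): "A single-centre experimental, prospective pilot study with non-probability sampling". The arms are defined by BMI at booking.
- **Size** (Statistics section): "we plan to recruit 15 women in each arm", taken from earlier studies with 14 per arm.

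The obese versus non-obese difference is a stated objective, listed after the assessment of process and of concentrations against the MIC.

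**The concern.** Each sample is fixed to a surgical event, not to a time after the dose. At incision the time since dose can differ by 30 min between two women who were both treated as planned. At closure the length of the operation is added.

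Plasma concentration after an intravenous dose depends strongly on that time. Because the groups are not randomised, nothing in the design balances the dose-to-incision interval or the operating time between them. A difference in mean concentration could therefore come from drug handling in obese women, from later or earlier sampling, or from both, and an ANOVA on group alone cannot say which.

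A second consequence needs no imbalance. Differences in timing between women enter the spread of the measured values. Inter-patient variability is in the study's title and is one of the reasons given for its size, so a spread that contains timing scatter would mislead the planning of the larger study.

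**Working it through.** **Inputs from the article.** 15 women per arm; 30–60 min from dose to incision; sampling at incision and closure; ANOVA by BMI group. The 15 per arm rests on precedent, with no error rate, power, effect size or SD, so there is no calculation to reproduce.

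**Assumed inputs (not in the article).** Plasma half-life 1.0–1.5 h with first-order decline; log-SD between women 0.25–0.5; closure at mean 100 min after dose with SD 15 min; obese arm sampled 0, 10, 15 or 20 min later.

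**Step 1: what a timing difference does to plasma concentration.** Proportional fall = 1 − 2^(−Δt / half-life).

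| Δt | half-life 1.0 h | half-life 1.5 h |
|---|---|---|
| 10 min | 10.9% | 7.4% |
| 15 min | 15.9% | 10.9% |
| 20 min | 20.6% | 14.3% |
| 30 min | 29.3% | 20.6% |

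For the full permitted window at 1.0 h: 1 − 2^(−0.5/1.0) = 1 − 0.707 = 0.293.

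**Step 2: what this does to the test.** Simulated closure samples, 15 per arm, the same elimination in both arms and no effect of obesity; two-group test on the concentrations at the 5% level. Ranges run over half-life 1.0–1.5 h.

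| Obese arm sampled later by | log-SD 0.25–0.35 | log-SD 0.5 |
|---|---|---|
| 0 min | about 5% | about 5% |
| 10 min | 8–17% | 6–8% |
| 15 min | 12–31% | 8–13% |
| 20 min | 18–50% | 11–19% |

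Across both columns the ranges are 6–17%, 8–31% and 11–50%. With time since dose in a linear model on log concentration, the rate returns to about 5%.

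**Step 3: a different timing model.** Dose to incision uniform on 30–60 min in both arms; incision to closure mean 45 min, SD 10 min; residual CV 20–40%; half-life 1.0–1.5 h. With the obese operation 15 min longer, the unadjusted ANOVA was significant in 12–44% of studies. With equal mean timing it was 4–6%. With adjustment it was 4.1–6.3% in all settings. The adjusted model fits the same log-linear decline that generated the data, so this shows that the remedy works when that form is right.

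**Step 4: inflation of variability without imbalance.** With k = ln 2 / half-life and timing SD 15 min = 0.25 h, the apparent CV is √(exp(s² + (0.25k)²) − 1), where s² = ln(1 + CV²). For a true CV of 25%, s² = ln(1.0625) = 0.0606.

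- Half-life 1.0 h: k = 0.693, (0.25k)² = 0.0300, apparent CV = √(exp(0.0906) − 1) = 31%.
- Half-life 1.5 h: k = 0.462, (0.25k)² = 0.0133, apparent CV = √(exp(0.0739) − 1) = 28%.

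**The case against.** The strongest reply is that the event is the point. The article compares concentrations at incision and closure because coverage at those moments is what matters. If obese women have longer operations and so less drug at closure, that is a real difference at closure, and adjusting for time would remove it. This stands. It is a reason to keep the event-based comparison and not to replace it. It does not help when the result is read as an effect of BMI on drug handling, which is how it would bear on dose adjustment.

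Other replies stand in part:

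- **The bias is conditional.** The article gives no dosing intervals or operating times by BMI. A reader might infer that obese women will be sampled later, or that the 30-minute window by itself biases the comparison. Neither is supported: with equal mean timing the error rate stays near 5%, and the window then adds only noise.
- **The PBPK work takes time into account.** A reader might infer that the PBPK check would inherit a biased ANOVA result. The article says otherwise: the model is to be compared with measured concentrations, not with the ANOVA result. Equally, neither that modelling nor the reporting of time above MIC is stated as an adjustment of the between-arm test.
- **Silence is not error.** A reader might add that the plan ignores skewness and the pairing of samples within a woman, or gives no estimate of variability. The article does not rule out a transformation or a repeated-measures form, and it states the aim of estimating variability. A condensed article may leave those details to the full protocol.
- **Adipose tissue may behave differently.** Drug may still be entering the tissue at incision, so the plasma decline cannot be carried over and even the direction of a timing effect is uncertain.
- **This is a pilot.** The main objective is process, and no success criterion uses the ANOVA. That lowers the priority but does not make the named test fit the sampling scheme.

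**Conclusion.** The point holds in a limited form. The article names a between-arm test with no time term, while its own dosing window and event-based sampling let time since dose vary between non-randomised groups. The test therefore cannot support a statement that obesity changes cefuroxime handling unless timing is shown to be alike or is adjusted for.

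The size depends on an undocumented timing difference. At 10 to 20 min it ranges from barely above the nominal 5% (6%, with 10 min and large variability) to one study in two (50%, with 20 min, small variability and the shorter half-life). These figures concern plasma at closure and assume first-order decline; no size is claimed for adipose tissue. The inflation of variability, from 25% to 28–31% in the example, needs timing scatter but no imbalance.

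This should be fixed before the analysis. It does not threaten the feasibility aims.

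**What to change.** 1. Keep the comparison at incision and closure, and the proportion above each MIC, as the description of coverage at those events.
2. Add, as the analysis used to attribute a difference to BMI, a linear model of log plasma concentration with arm (or BMI), actual minutes since dose, and dose if it varies. Include a random effect for woman when occasions are combined.
3. Report the geometric mean ratio and the between-woman CV, each with a 95% CI, and tabulate dose-to-sample times by arm.
4. For adipose tissue, fit the same model by sampling occasion without assuming that concentration falls with time.
5. Confirm that the CS procedure form captures the clock time of each sample. The form is in the supplement and was not available, so this is a check and not a stated gap.

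Cost: one or two degrees of freedom out of 30 women, a few lines of wording and a little more analysis. No extra patients or samples are needed, and dose time is already recorded. If timing differs greatly between the arms, the adjusted interval will be wider, which correctly shows how little the data can then say about BMI alone.
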